### Recording Subject Withdrawals

In the event of a subject withdrawal, the following information must be recorded in the Case Report Form (CRF):

1. Date of withdrawal

2. Reason for terminating participation in the study

3. Last treatment date

4. Follow-up assessments

The Investigator should continue to follow-up all serious adverse events or other adverse events that are considered to be related to the study drug, until they are resolved or assessed to be chronic or stable by the Investigator. This should be documented in the subject's medical records. This follow-up may be extended beyond the end of the study period.

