**4) Lipoaspiration and isolation of ADSCs-SVF: **All eligible patients will undergo lipoaspiration under general anesthesia in a sterile surgical operating room setting. 50 mL of blood in EDTA will be taken to prepare platelet rich plasma (PRP). Approximately 100 - 500 gr of adipose tissue will be isolated from the above procedure performed by a plastic surgeon. Enzyme dissolution procedure of the adipose tissue, using collagenase type I solution under agitation for 2 hours plus 10 cc of lecithine followed by two centrifugations at 100 g for 10 minutes the first and at 1800 g for 10 minutes the second, will be performed to separate the stromal cell fraction (pellet) from adipocytes. The pellets will be treated with red lysis buffer. The final pellet will be re-suspended and a small volume of suspension will be used for flow cytometry analysis, counting CD29, CD73, CD90, CD34, CD105, positive cells and CD14, CD31 and CD45 negative cells in Coulter Epics XL/MCL. 10 mL of the suspension will be used for bacterial check with the BacT/Alert system (with colorimetric carbon dioxide detector). In the case of an infected sample the microorganism will be identified with VITEK 2 Compact 15 and will be excluded. A volume of DMSO solution will be added in the remaining suspension so that the final volume contains 10% DMSO and 2% Haes-steril 200. The cells will be cryo-preserved gradually and stored in cryovials, air-tightly sealed with cryoflex membrane. The vials will be placed in constant temperature in liquid nitrogen and will be stored there. Viability of the cells will be estimated by tryphan blue. A total of 3-5 × 10^6 ^cells per gram of adipose tissue is expected to be isolated. Based on the current literature [29], since SVF represents an heterogeneous cell population it is anticipated that approximately 50-70% of the total number of isolated cells to be of mesenchymal origin meaning CD29, CD105, CD90, CD73 positive and CD34, CD45 negative cells and 20-30% mature endothelial (CD31 and positive) and hematopoetic (CD34 positive) cells.

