### Primary end-points (Safety and Toxicity levels)

The procedure is safe and well tolerated by the patients, as reflected by the absence of signs compatible with infection, allergic reaction, disease acute exacerbation, and ectopic tissue formation, at 12 months after the first post-endobronchial infusion of SVF cells (total follow-up duration for each patients = 12 months).

In particular, patients will be subdivided into three categories depending on the level of toxicity, defined as:

**1) Low level**, including minor side effects such as increased cough, low fever (less than 37.5°C, skin allergic reactions)

**2) Medium level**, including non-life threatening allergic reactions, infections that do not require hospitalization, elevation of liver enzymes or creatinine serum levels.

**3) High level**, including death and/or life threatening major adverse events such as disease acute exacerbations defined as follows:

*a) *If the patient experiences a significant worsening of dyspnea and a decline in exercise tolerance associated with a 10% decrement of their FVC, a 10 mmHg change in PaO_2 _or 50% increase in their oxygen requirement, and a significant progression in their radiographic score between the three month clinic visits;

*b) *If the patient needs to be admitted to the hospital because of worsening respiratory failure requiring mechanical ventilation, worsening gas exchange, or presumed pulmonary infection.

*c) *If the patient develops ectopic tissue formation compatible with carcinogenesis as assessed by whole body computed tomography at 12 months after the first post-endobronchial infusion of SVF cells

Exploratory secondary end-points:

1) Assessment of Forced Vital Capacity (FVC%) predicted.

2) Assessment of Diffuse Lung Capacity for carbon monoxide (DL_CO_%) predicted.

3) Assessment of 6MWT.

4) Assessment of dyspnea scales (Borg, MRC) as well as health-related quality of life questionnaires (SGRQ)

5) Assessment of the disease extent and severity as reflected by chest high resolution computed tomography (HRCT) at 6 and 12 months post-bronchoscopy.

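### After withdrawal, a non-serious adverse event must be followed only if judged related to an undefined study drug, although the primary safety end-point sets no attribution condition

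*Protocol article*

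**What the plan says.** The rule stands in the Protocol article under Recording Subject Withdrawals. The events that the investigator is to keep pursuing are "all serious adverse events or other adverse events that are considered to be related to the study drug". Pursuit ends once the investigator judges the event resolved, chronic or stable. The next sentences ask for documentation in the medical records and allow this follow-up to run past the end of the study. The same section lists what goes into the case report form at withdrawal: date, reason, last treatment date and follow-up assessments. That list has no causal filter.

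The primary end-point (Primary end-points, Safety and Toxicity levels) is worded for the procedure: "The procedure is safe and well tolerated by the patients, as reflected by the absence of signs compatible with infection, allergic reaction", and then acute exacerbation and ectopic tissue formation, assessed 12 months after the first infusion ("total follow-up duration for each patients = 12 months"). It then sorts patients into Low, Medium and High toxicity. None of the three definitions asks whether the event was caused by the product.

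Study Methodology describes more than an infusion of cells. Under item 4, "All eligible patients will undergo lipoaspiration under general anesthesia", and under item 8 the cells are given by flexible bronchoscopy, repeated at monthly intervals.

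**The concern.** The end-point and the follow-up rule use different tests. The end-point looks for signs of certain events and grades them without asking about cause. The follow-up rule, for non-serious events, makes the investigator's view of cause decide whether an open event is pursued once the patient has withdrawn.

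This matters because the toxicity scale allows an event to move up. A non-serious infection is Medium, and it becomes High if it later leads to hospital admission. Worsening dyspnoea put down to IPF becomes High if the decline in function and the radiographic progression meet the stated criteria. If no one is obliged to follow the open event, such a rise could be missed. Any such loss would favour a finding that the procedure is safe and well tolerated, which is the question the trial was set up to answer.

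The rule is also unclear in two places. The study drug is not defined, and the sentence can be read so that relatedness limits serious events as well.

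**Working it through.** The plan states no figure on this point, so the check is mainly textual.

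**Step 1. What the rule covers.** Events open at withdrawal, by seriousness and judged cause:

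| Event | Judged cause | Duty to follow |
|---|---|---|
| Serious | any | Yes on the natural reading; only if drug-related on the alternative reading |
| Non-serious | infused product | Yes |
| Non-serious | bronchoscopy or lipoaspiration | Not settled, because study drug is undefined |
| Non-serious | IPF | None stated |

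The article uses four terms for what is given: study drug (Recording Subject Withdrawals), investigational drug (Study Duration & Termination), and test drug and IP (Discontinued/withdrawn). None is said to include or exclude the procedures.

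**Step 2. What the end-point covers.**
- Low: increased cough, low fever, skin reactions. These are non-serious.
- Medium: allergic reactions that do not threaten life, infections managed without admission, raised liver enzymes or creatinine. These are largely non-serious.
- High: death and life-threatening events, including acute exacerbation, respiratory admission and ectopic tissue. These are serious, and acute exacerbation is itself an IPF event.

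The end-point therefore counts disease events without asking about cause, while the last row of the table places no duty to follow non-serious ones after withdrawal.

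**Step 3. Who could be affected.** Discontinued/withdrawn gives five circumstances.
- Death: nothing remains to follow.
- Intolerable toxicity during infusion: likely to be judged related, so mostly inside the rule.
- Withdrawal of consent: further contact may not be possible under any wording.
- Investigator's discretion: the main route to an open, non-serious event judged unrelated.
- Screening error before the product is given: the patient may already have had lipoaspiration, and an open non-serious surgical or anaesthetic event cannot be caused by cells never infused. This patient may also lie outside the 12-month end-point, which runs from first infusion.

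The group is narrow. No withdrawal, event or progression rate is given from which to size it.

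**Step 4. Scale only.** Take n = 12 (Study Duration & Termination) and assume all 12 stay in the denominator. The exact two-sided 95% upper limit p for x events solves P(X ≤ x | 12, p) = 0.025.
- x = 0: (1 − p)^12 = 0.025, so p = 1 − 0.025^(1/12) = 26.5%.
- x = 1: (1 − p)^12 + 12p(1 − p)^11 = 0.025, so p = 38.5%.

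One event not seen would lower the upper limit by 38.5 − 26.5 = 12.0 percentage points. This holds for any single missed event in 12 patients and does not say how likely one is under this rule.

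**The case against.** The strongest reply is that the sentence only says how long certain events are pursued. It does not govern detection, recording, grading or counting. Events recorded before withdrawal stay in the data, and follow-up assessments of withdrawn subjects go into the case report form without regard to cause. This stands. A reader might infer that events ascribed to bronchoscopy, lipoaspiration or IPF are dropped from the safety data, but no sentence says so.

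Second, on the natural reading all serious events are followed whatever the cause, so death, acute exacerbation and respiratory admission are covered, and an event that worsens to High enters that limb. This largely stands. What remains is that an event must be known to have become serious, and for an open non-serious event judged unrelated the rule requires no one to keep looking.

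Third, the contrast with the end-point is softer than it looks. The end-point speaks of toxicity and side effects, which hint at cause, and the Aim and hypothesis section uses procedure for the endobronchial infusion, so lipoaspiration may not belong to it. Nor is bronchoscopic delivery said to be outside the study drug. Both points stand, so only the IPF case follows directly from the text; the other two are possible.

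Finally, following serious and related events to resolution is a common rule, and a condensed article may leave adverse-event detail to the full protocol. But this article does state a rule, and the point concerns its mismatch with the stated end-point.

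**Conclusion.** The point holds as a modest mismatch between two stated rules. Follow-up of non-serious events after withdrawal depends on judged relatedness to an undefined study drug, while the primary end-point covers 12 months from first infusion with no attribution condition and relies on largely non-serious events for its Low and Medium levels. A later rise in level of an open event put down to IPF, or possibly to bronchoscopy or lipoaspiration, could go unseen. Whether relatedness also limits serious events needs to be stated.

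This rests on the natural reading of the sentence and on at least one patient withdrawing with such an event open. The likely number is small and cannot be estimated from the document. A reader might take the gap between 26.5% and 38.5% as the size of a bias in the safety conclusion. The document does not support that: those figures show only what one event in 12 is worth, and nothing shows that one would be missed.

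**What to change.** Reword the sentence under Recording Subject Withdrawals along these lines: where the patient consents, all adverse events open at withdrawal, serious or not and whatever the judged cause, are followed until resolved, chronic or stable, and those still open are followed at least to month 12 after first infusion; they are graded by the Low, Medium and High levels of the primary end-point. Month 12 should be a minimum and not a cut-off, so the existing provision for follow-up beyond the study period should be kept. For a patient never infused, month 12 has no starting point and the first limb alone applies.

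Record attribution separately (product, bronchoscopy, lipoaspiration or anaesthesia, IPF) as description and not as a filter. With relatedness removed as a condition, the doubt about serious events disappears and the undefined term no longer decides who is followed.

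The cost is a reworded sentence, a few extra contacts in at most 12 patients, and a slightly higher event count that includes background IPF events. The change concerns data collection and alters no treatment.

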### Replacement of Subjects Withdrawn

Subjects who are prematurely withdrawn from the study will not be replaced.

## Discussion

Currently, the application status of MSCs as treatment modalities in IPF is still in its infancy and remains exploratory. Although a number of safety and efficacy clinical trials of MSCs as therapeutic options in immune-mediated and cardiac diseases have already been published with tantalizing results, to our disappointment, pulmonary and critical care medicine have traditionally lagged behind other therapeutic and research fields including hematology, gastroenterology and cardiology in translational studies of the use of reparative cells [21-23,33,34]. Standing in front the dilemma something or nothing the agony and at the same time desire of chest physicians to test novel therapeutic options for patients with IPF is clearly understandable. MSCs and especially ADSCs may provide an ethically uncontested, cost-effective, easily accessible and well tolerated therapeutic option in the hands of chest physicians in the following years. For these cell-based therapies to become truly evolutionary there is only one approach: phase I safety clinical trials followed by large multicenter randomized controlled efficacy clinical trials [21].

Nevertheless safety concerns mainly arising from IPF pathogenesis that is still elusive and controversial coupled with issues reflecting the origin and the minimal potential of ADSCs to differentiate into fibroblastic colony forming units have severely hampered clinicians' efforts to apply, so far, cell-based therapies for the treatment of this fatal disease [35,36].

To address the above concerns and to establish a rigid basis for future efficacy clinical trials we propose for the first time in the therapeutic field of IPF a protocol referring to a phase Ib nonrandomized clinical trial to evaluate safety and feasibility of endobronchial infusion of autologous ADSCs-SVF in patients with IPF of mild to moderate disease severity. Original protocol has already been approved by the Local Ethics and Scientific Committee of the University Hospital of Alexandroupolis, Democritus University of Thrace, Greece (reference number EHD33/1SC/16-02-2010) with the title "A prospective, unicentric, non randomized, phase I clinical trial to study the safety of the adipose-derived adult stromal vascular fraction cells as a therapeutic agent in Idiopathic Pulmonary Fibrosis".

So far preliminary data recently presented at the 21^ST ^European Respiratory Society Congress, Amsterdam 2011 in the form of an abstract seem promising and intriguing since none of the 12 patients enrolled in the study experienced any clinically significant cases of infections, allergic reactions, acute exacerbations or other major side effects requiring hospitalization. In addition 6 months follow-up data revealed a marginal improvement at 6MWD and FVC levels [21,37].

The main purpose of this project and consequently this trial is to provide worldwide scientific committee with pivotal safety data regarding this novel therapeutic option and accelerate its application to a larger cohort of patients in the context of multicenter phase II and III clinical trials. There is plenty of room for further technical improvements, development and widespread acceptance and accessibility. However, pilot safety studies are of major importance and represent the first hamper that should be overcome to establish a rigid basis for larger clinical trials where safety concerns will be addressed cautiously and thoroughly and efficacy outcomes of high scientific rigidity will be safely extracted.

## Abbreviations list

6MWT: 6-minute walking test; ABGs: Arterial blood gases; ADSCs: Adipose-derived stem cells; BM-MSCs: Bone Marrow-Mesenchymal Stem Cells; CAT: Cough Assessment Test; CRF: Case Report Form; DL_CO_: Diffusing lung capacity for carbon monoxide; ECG: Electrocardiogram; FVC: Forced Vital Capacity; HGF: Hepatocyte Growth Factor; HRCT: High Resolution Computed Tomography; IGF: Insulin-like Growth Factor; KGF: Keartinocyte Growth Factor; IPF: Idiopathic Pulmonary Fibrosis; PFTs: Pulmonary Function Tests; PRP: Platelet Rich Protein; SDF: Stromal derived Factor; SGRQ: Saint George's Research Questionnaire; SVF: Stromal Vascular Fraction; UIP: Usual Interstitial Pneumonia, VEGF: Vascular Endothelial Growth Factor.
